**Procedure**

**Time and content of information collection**

1 Registration Information (11-13+6)

1.1 Demographic characteristics and medical history of pregnant women (risk factors)

1) Age, race, height, weight, gestational age (CRL calculation method), occupation;

2) Method of pregnancy (natural pregnancy, assisted reproductive technology - using ovulation drugs or in vitro fertilization);

3) Smoking history;

4) History of chronic hypertension;

5) History of type I or type II diabetes;

6) History of kidney disease;

7) Abnormal pregnancy history (21/18-trisomy, NTD, unknown abortion history, gestational diabetes, etc.);

8) History of preeclampsia;

9) Family history of preeclampsia (mother or sister);

10) History of autoimmune disease (systemic lupus erythematosus or antiphospholipase syndrome);

11) Previous pregnancy history and parity;

12) The interval between pregnancies;

13) Systolic blood pressure ≥130 mmHg or diastolic blood pressure ≥80mmHg;

14) The presence of hypertension risk factors such as obstructive sleep apnea;

15) Previous prenatal diagnosis experience (villus biopsy/amniotic fluid puncture).

1.2 Laboratory Examination

Folic acid, vitamin B12, fasting blood glucose, blood routine, urine routine, kidney function, blood lipid, coagulation function, liver function, thyroid function.

1.3 Physical examination

Blood pressure and BMI (height and weight) at 11-13+6 weeks of pregnancy.

1.4 Ultrasonic examination

Uterine artery pulse index, head and hip length, NT at 11-13+6 weeks of pregnancy.

1.5 Serum marker examination

Placental growth factor (PLGF) at 11-13+6 gestational weeks.

1.6 Baseline of primary outcomes

24-hour ambulatory blood pressure, ActiGraph WGT33-BT exercise accelerometer to monitor exercise intensity and energy metabolism.

**Follow-up data registration (middle and late pregnancy)**

2.1 Primary outcomes

24-hour ambulatory blood pressure, ActiGraph WGT33-BT exercise accelerometer to monitor exercise intensity and energy metabolism.

2.2 The presentation of preeclampsia

Systolic blood pressure ≥140mmHg and/or diastolic blood pressure ≥90mmHg after 20 weeks of gestation, accompanied by any of the following: urinary protein quantity ≥0.3g/24h, or urinary protein/creatinine ratio ≥0.3, or urinary protein ≥ (+); or accompanied by following damages of organs involved: heart, lung, liver, kidney and other important organs, or abnormal in the digestive system, nervous system, placenta - fetal involvement, etc.

**Severe pre-eclampsia refers to a pregnant woman with one of the following symptoms:**

1) Uncontrolled blood pressure: systolic blood pressure ≥160mmHg and/or diastolic blood pressure ≥110mmHg;

2) Persistent headache, visual disturbance, or other central nervous system abnormalities;

3) Persistent upper abdominal pain, subcapsular hematoma or liver rupture;

4) Elevated serum alanine aminotransferase (ALT) or aspartate aminotransferase (AST) levels;

5) Impaired renal function: urinary protein content > 2.0g/24h; oliguria (24h urine volume < 400ml, or < 17ml/hour), or serum creatinine level > 106μmol/L;

6) Hypoproteinemia with ascites, pleural effusion or pericardial effusion;

7) Platelet count decreased and lower than 100×10^9^/L; hemolysis, anemia, elevated lactate dehydrogenase (LDH), or jaundice;

8) Heart failure;

9) Pulmonary edema;

10) Fetal growth restriction or oligohydramnios, fetal death, placental abruption, etc.

2.3 Laboratory examination

Fasting blood glucose, blood routine, urine routine, kidney function, coagulation function, liver function, thyroid function.

2.4 Physical examination

Blood pressure, height, weight.

2.5 Ultrasound Examination

Crown-rump length, double parietal diameter, umbilical artery pulse index, umbilical artery resistance index, umbilical artery S/D ratio.

2.6 Screening of serum markers

Serum placental growth factor (PLGF) at 26-27+6 weeks and 32-36+6 weeks.

2.7 Medication compliance

Take the medication prescribed by the doctor at each follow-up visit, and make statistics on the number of drugs taken.

2.8 Other

Abdominal circumference

**Data Management**

An electronic collection and management system is proposed for this study, in which researchers are responsible for the collection of primary data and for organizing the entry of case report information into a spreadsheet. The problems found in the process of data management will be notified to the researchers in the form of a query form, and the researchers will review and give feedback to the questions as soon as possible. The feedback records will be saved as the basis for data modification. After the case review is completed, the data will be locked, and the locked data files are not allowed to be changed.

**Statistical Analysis**

**Data quality assessment and data clearing**

The research requires evaluating whether the integrity, accuracy and consistency of data meet the pre-set quality requirements, and clearing up the duplicate data and unqualified data to form usable data.

**Data analysis**

The study is powered for the primary outcome measure of change in 24-hour ambulatory SBP from the first to the third trimester. The sample size calculation was based on the results of Lopes S et al.[14], who showed a decrease of -7.3 ± 12.7mmHg in 24-hour ambulatory SBP in the exercise group with 1.1 ± 8.2mmHg in the control group. A sample of 72 pregnant women (36 per group), with a two-sided significance level of 0.05, provided 90% statistical power to demonstrate this difference in 24-hour ambulatory SBP. In order to accommodate a 20% attrition rate, 90 pregnant women will be recruited (PASS11, independent t-tests; allocation ratio = 1).

Continuous variables will be presented as means ± standard deviations or median (interquartile range) according to normal distribution or not. Between-group differences at baseline will be tested with Student’s independent t-test or Mann–Whitney U test. For the categorical variables, results will be expressed as counts and percentages. Categorical variables will be tested with the chi-square test or Fischer test if appropriate between groups at baseline. The assessment of compliance with daily physical activity and safety will be summarized for the two groups. A cut-off of 80% of baseline physical activity during the second and third trimesters will be used to determine compliance well. Adverse events, if any, will be reported. The primary outcome and difference of the change in 24-hour ambulatory SBP from the first to the second trimester between groups will be analyzed using analysis of covariance, adjusting for baseline blood pressure. Other secondary outcomes will be analysis using general linear modelling to compare the difference of blood pressure change in the MPA and LPA groups at the second and third trimesters, adjusting for baseline blood pressure. The analyses will be conducted based on the intention-to-treat principle. The intention-to-treat population will comprise all the patients with the exception of those who do not complete ambulatory blood pressure measurement and physical activity monitoring at 3-time points for any reason, such as miscarriage, or preterm birth. Per-protocol set will be performed as a sensitivity analysis. Relative risks and 95% confidence intervals will also be provided. A two-sided p-value below 0.05 will be considered statistically significant in all analyses. Data will be analyzed using SPSS 25 statistical software.

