**Grouping scheme**

1. Grouping method: During early pregnancy (11~13+6 weeks), an ActiGraph wGT3X-BT exercise accelerometer will be worn on the wrist to monitor the intensity, time, number of steps and energy metabolism of daily physical activity within 1 week, and the number of exercise steps will be collected by mobile phone APP. Participants will be divided into light and moderate groups according to the activity intensity of early pregnancy. Moderate-intensity activity is defined as 150 minutes per week, and the light-intensity activity group has a activity intensity or activity time of fewer than 150 minutes per week.

2. Drug intervention plan: pregnant women in both groups take low-dose aspirin 100mg daily from 11 to 13+6 gestational weeks until 2 to 7 days before termination or 34 gestational weeks as recommended by the guidelines. Oral calcium supplementation should be at least 1 g/ day.

3. Health guidance: limit salt intake (<6 g/d), smoking cessation, regular rest, weight control, etc.

4. Exercise monitoring: Wear an ActiGraph wGT3X-BT exercise accelerometer on wrist to monitor physical activity for a week. Except for bathing, swimming and other contacts with water, the rest of the time should be worn as required, ensure that more than 10 hours of wear every day, and at least two working days (Monday to Friday), rest day (Saturday to Sunday) with one day of valid data.

1) Activity intensity: light physical activity (100 -1952 CPM) and moderate physical activity (≥1952 CPM). Data were collected by ActiLife 6.0 analysis software after completion.

2) Active metabolic rate: measured by average metabolic equivalents (METs).

3) Perceived exertion rating: ratings of perceived exertion (RPE) based on the Borg perceived Exertion Scale (Table 1) are used. The Borg scale has 15 ratings ranging from 6 to 20, representing different levels of fatigue, with 6 being "very, very easy" and 20 beings "very, very difficult". For moderate-intensity exercise, the RPE score of pregnant women should be 13 to 14 points, that is, the feeling of self-exercise intensity is somewhat difficult.

[figure not shown]

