**Outcomes**

1. Primary outcome: the difference in 24-hour ambulatory systolic blood pressure change from baseline during the third trimesters of pregnancy;

2. Secondary outcomes: the difference in 24-hour ambulatory systolic blood pressure change from baseline during the second trimesters of pregnancy; the difference of daytime and nighttime ambulatory blood pressure, daytime and nighttime and 24-hour diastolic blood pressure, and clinic blood pressure changes from baseline;

3. Exploratory outcomes: incidence of preeclampsia; effect of exercise on blood pressure control in pregnant women with preeclampsia

4. Safety outcomes: activity tolerance decline rate; incidence of shortness of breath; incidence of heart failure;

5. Other relevant outcomes: severe complications of preeclampsia (eclampsia, heart failure, pulmonary edema, HELLP syndrome, DIC), fetal death, iatrogenic premature delivery, neonatal asphyxia, NICU. Compliance with oral aspirin and calcium; mobile phone exercise recording monitoring exercise intensity compliance; the Subjective Exertion Scale (RPE) monitors an individual's exercise intensity tolerance.

[figure not shown]

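### Activity groups are self-selected, but the blood pressure models adjust only for baseline blood pressure and the relative risks for nothing stated, so the group difference cannot be read as the influence of activity

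*Supplement*

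**What the plan says.** All references are to the chronic hypertension protocol in the Supplement.

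- **How groups arise.** Grouping scheme, item 1: "Participants will be divided into light and moderate groups according to the activity intensity of early pregnancy". The boundary is set by this sentence: "Moderate-intensity activity is defined as 150 minutes per week". No randomisation is described.
- **Primary model.** Data analysis: the primary outcome (change in 24-hour ambulatory systolic pressure to the third trimester) and the corresponding second-trimester change "between groups will be analyzed using analysis of covariance, adjusting for baseline blood pressure".
- **Other secondary outcomes.** General linear models compare "blood pressure change in the MPA and LPA groups at the second and third trimesters, adjusting for baseline blood pressure".
- **Relative risks.** "Relative risks and 95% confidence intervals will also be provided", with no covariates named.
- **Baseline comparability.** "Between-group differences at baseline will be tested with Student’s independent t-test or Mann–Whitney U test", with chi-square or Fisher tests for categorical variables. Nothing says what follows from a difference.
- **What is recorded at registration.** Procedure 1.1 begins with "Age, race, height, weight, gestational age (CRL calculation method), occupation" and goes on to smoking, kidney disease, previous preeclampsia and parity. Section 1.3 adds BMI.

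The only sensitivity analysis named is the per-protocol one. No wider multivariable adjustment, matching, propensity score or weighting appears anywhere in the protocol.

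**The concern.** The Background closes by stating that the study explores how physical activity influences blood pressure in these women, and one exploratory outcome is worded as the "effect of exercise on blood pressure control in pregnant women with preeclampsia". Both lean towards a causal reading. The analysis, however, is of a kind that suffices when exposure has been assigned at random: a two-group comparison with the baseline value of the outcome as sole covariate.

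Women who reach the activity threshold by their own choice may well differ in age, weight, parity, smoking and medical history. The protocol itself files most of these under a heading that calls them risk factors, and its Background lists smoking cessation and weight reduction beside physical activity as lifestyle measures for hypertension. Baseline blood pressure absorbs what acts through the starting level. It does not absorb factors that change how blood pressure moves between the first and third trimesters, and that movement is the primary outcome. Testing such factors at baseline without carrying them into a model describes the imbalance and leaves it in the estimate. A larger sample would only estimate the confounded contrast more precisely.

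**Working it through.** **1. The plan's own figure.** Inputs from Data analysis: change of −7.3 (SD 12.7) against 1.1 (SD 8.2) mmHg, two-sided α = 0.05, power 90%, 1:1 allocation, 20% attrition.

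- Difference: 1.1 − (−7.3) = 8.4 mmHg.
- Root-mean-square SD: √((12.7² + 8.2²)/2) = √(228.53/2) = 10.69 mmHg.
- Noncentral t: power is 0.8998 at 35 per group and 0.908 at 36, so 36 per group, 72 in total.
- Attrition: 72/0.80 = 90.

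The stated 72 and 90 reproduce. The arithmetic of the sample size is not the issue.

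**2. Planned precision.** SE of the difference = √(12.7²/36 + 8.2²/36) = √(228.53/36) = 2.52 mmHg.

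**3. What a residual bias would do.** Suppose activity has no effect but unadjusted factors shift the group difference by *b* mmHg. The test statistic is then noncentral t on 70 df with noncentrality *b*/2.52, and the chance of p < 0.05 is:

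| Assumed bias *b* (mmHg) | *b*/2.52 | Chance of a significant result |
|---|---|---|
| 0 | 0 | 0.05 |
| 1 | 0.40 | 0.07 |
| 2 | 0.79 | 0.12 |
| 3 | 1.19 | 0.22 |

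The values of *b* are assumptions; the documents supply none. For scale, one confounder differing by 0.5 SD between groups, with partial correlation 0.3 with the change in pressure (both assumed), gives 0.5 × 0.3 × 10.69 = 1.6 mmHg and a rate of about 0.10. The SE is that of the planned t-test with equal groups; the ANCOVA's SE may differ.

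**4. Which recorded variables reach a model.**

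| Variable | Recorded at registration | In any stated model |
|---|---|---|
| Baseline blood pressure | Yes (1.3, 1.6) | Yes, except for relative risks |
| Maternal age | Yes (1.1) | No |
| BMI | Yes (1.3) | No |
| Parity, prior preeclampsia | Yes (1.1) | No |
| Smoking, kidney disease | Yes (1.1) | No |
| Baseline antihypertensive use | Not listed (1.1–1.6) | No |

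**5. Price of adjusting.** If six added covariates explain a share R² of group membership and no outcome variance, the SE becomes 2.52/√(1 − R²). Power for 8.4 mmHg with 36 per group (df = 72 − 2 − 6 = 64), and the size that restores 90%:

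| R² | SE (mmHg) | Power | Evaluable for 90% | Recruited (÷ 0.80) |
|---|---|---|---|---|
| 0 | 2.52 | 0.907 | 72 | 90 |
| 0.10 | 2.66 | 0.876 | 78 | 98 |
| 0.20 | 2.82 | 0.836 | 88 | 110 |
| 0.30 | 3.01 | 0.784 | 100 | 125 |

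Outcome variance explained by the covariates works the other way: a share R²_Y multiplies the SE by √(1 − R²_Y), so R²_Y equal to R² cancels the loss.

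**The case against.** The strongest reply is that much confounding is already limited. The exclusion criteria remove pregestational diabetes, severe cardiovascular or respiratory disease, hyperthyroidism, recurrent abortion and prior spontaneous preterm birth. Both groups get the same aspirin, calcium and health guidance. Analysing change with baseline pressure as covariate removes confounding that acts through the starting level. All of this stands and narrows the problem to factors that affect the trajectory of blood pressure. It leaves age, BMI, parity, prior preeclampsia, smoking and kidney disease open.

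One might also say that covariates are a matter for a separate analysis plan. That carries little weight here, because Data analysis names an adjustment set and stops at one variable.

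Several stronger readings are tempting, and the documents do not support them:

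- *The study will report confounding as an effect of activity.* The plan prescribes no wording for its conclusion. The primary outcome is a difference in change, and the aim is framed as exploratory. What can be shown is a risk of over-interpretation.
- *Type I error is uncontrolled.* Nothing shows the test of whether the groups differ to be invalid. The trouble arises when its p-value is used to answer a causal question.
- *False-positive rates of 25% or 48%.* These need two or three confounders of 1.6 mmHg each (3.2 or 4.8 mmHg in total), independent of one another and all acting in the same direction. Age, parity, BMI and obstetric history plausibly overlap, so these figures are worst case.
- *The remedy uses only data in hand.* This is true of the variables above but not of baseline antihypertensive use, which is missing from the listed registration items. Gestational age at follow-up monitoring is measured after exposure and is not a baseline confounder.

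**Conclusion.** The point holds as a gap in the stated adjustment. In a comparison of self-selected groups, the primary and secondary blood pressure models adjust for baseline blood pressure alone, the relative risks for nothing stated, and likely confounders already being collected are unused. The resulting difference cannot be read as the influence of physical activity.

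Its size is unknown. The 7–22% range rests on an assumed residual bias of 1 to 3 mmHg, the plan's own SDs, 36 women per group and no true activity effect. It shows how exposed the primary test is; it does not demonstrate a bias, and the direction could be either way. The gap should be closed before analysis because it affects the primary estimate and costs little to mend.

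**What to change.** In Data analysis, pre-specify one small covariate set for the primary and secondary models, chosen on subject-matter grounds and not from the baseline p-values. An example is baseline systolic pressure (or the baseline value of the outcome concerned), maternal age, first-trimester BMI, parity and prior preeclampsia, smoking and kidney disease. Add baseline antihypertensive use only if it is recorded; that would need a new item on the registration form.

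Adjust the relative risks where event counts allow, and otherwise label them unadjusted. State that conclusions will be worded as adjusted associations. A propensity-weighted sensitivity analysis on the same covariates is optional, given about 72 evaluable women.

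The cost is a change of model specification and some precision, as set out in the working: power of about 0.88 to 0.78 instead of 0.91 if the covariates explain 10–30% of group membership and nothing of the outcome. Holding 90% power in those cases would take 98 to 125 recruited women instead of 90. Any outcome variance the covariates explain reduces that cost.

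### The primary ANCOVA pools one residual variance, though the planning SDs differ (12.7 vs 8.2 mmHg) and nothing secures the 1:1 split; if the groups are unbalanced and those SDs carry over, its standard error is miscalibrated

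*Supplement*

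**What the plan says.** All references are to the later of the two protocols in the Supplement, on pregnant women with chronic hypertension.

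- **Planning figures** (Data analysis). The sample size rests on a cited exercise trial, "who showed a decrease of -7.3 ± 12.7mmHg in 24-hour ambulatory SBP in the exercise group with 1.1 ± 8.2mmHg in the control group". The calculation uses an independent t-test with an allocation ratio of 1 and claims a power of 90%. Its size is given as follows: "A sample of 72 pregnant women (36 per group), with a two-sided significance level of 0.05". Recruitment is then raised for attrition: "In order to accommodate a 20% attrition rate, 90 pregnant women will be recruited".
- **How the groups arise** (Grouping scheme). Women are classed as light or moderate from one week of accelerometry at 11 to 13+6 weeks, with a cut at 150 minutes per week. No randomisation, quota or stratified recruitment is described.
- **Primary model** (Data analysis). The change in 24-hour SBP "between groups will be analyzed using analysis of covariance, adjusting for baseline blood pressure".
- **Other blood pressure outcomes** (Data analysis). "Other secondary outcomes will be analysis using general linear modelling to compare the difference of blood pressure change in the MPA and LPA groups", again adjusted for baseline.
- **Decision rule** (Data analysis). "A two-sided p-value below 0.05 will be considered statistically significant in all analyses".

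The section mentions no robust standard error, no unequal-variance option and no check of the variance assumption for these models.

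**The concern.** Ordinary ANCOVA estimates one residual variance and applies it to both groups. With equal group sizes, unequal variances do little harm, because the pooled figure averages them with the right weights. With unequal sizes the pooled figure is dominated by the larger group. If the smaller group is the more variable one, the standard error is too small and false positives rise. If the larger group is the more variable one, the standard error is too large, and power is lost.

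The planning SDs are clearly unequal, and the split depends on how active the recruited women happen to be. It can shift again at analysis, because women without ambulatory blood pressure and activity monitoring at all three time points leave the analysis set. At stake are the p-value and confidence interval of the primary comparison.

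**Working it through.** **Inputs from Data analysis.** Change SD 12.7 (exercise) and 8.2 (control); means -7.3 and +1.1; 36 per group; two-sided 5%; 20% attrition.

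**Assumptions.** The documents give no expected split, so a range is shown. The planning SDs are taken as residual SDs, with 12.7 in the moderate group.

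**Step 1. Reproduce the plan's sample size.** Difference = 1.1 − (−7.3) = 8.4 mmHg. Pooled SD = √[(161.29 + 67.24)/2] = √114.27 = 10.69. The noncentral t distribution gives power 0.8998 at 35 per group and 0.908 at 36, so 36 is the smallest size reaching 90%. Attrition: 72/0.8 = 90. The plan's figures reproduce.

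**Step 2. Variance ratio.** 12.7²/8.2² = 161.29/67.24 = 2.40 (SD ratio 1.55).

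**Step 3. Model standard error against true standard error.** With n₁ moderate and n₂ light:

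- True variance of the difference = 161.29/n₁ + 67.24/n₂
- Variance used by the pooled model = {[(n₁−1)·161.29 + (n₂−1)·67.24]/(n₁+n₂−2)} × (1/n₁ + 1/n₂)

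At 18:54 the true variance is 8.961 + 1.245 = 10.206 (SE 3.195). The pooled variance is (2741.93 + 3563.72)/70 = 90.08, times 0.07407 = 6.673 (SE 2.583). The ratio is 2.583/3.195 = 0.81. The nominal critical value 1.96 therefore acts as 1.96 × 0.809 = 1.585, a two-sided error of about 11.3%.

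At 36:36 both variances equal 228.53/36 = 6.348, so the ratio is 1.00.

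At 54:18 the true variance is 2.987 + 3.736 = 6.722 (SE 2.593). The pooled variance is (8548.37 + 1143.08)/70 = 138.45, times 0.07407 = 10.256 (SE 3.202). The ratio is 1.24.

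**Step 4. Simulation of the ANCOVA itself.** 72 women, no group effect, common baseline slope, 40,000 runs per split:

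| Moderate:light | Model SE / true SE | Type I error, ordinary ANCOVA | Type I error, HC3 |
|---|---|---|---|
| 18:54 (1:3) | 0.81 | 11.1% | 5.3% |
| 24:48 (1:2) | 0.87 | 8.5% | 4.7% |
| 29:43 | 0.92 | 7.1% | 4.8% |
| 36:36 (1:1) | 1.00 | 5.0% | 4.5% |
| 43:29 | 1.09 | 3.5% | 4.6% |
| 48:24 (2:1) | 1.15 | 2.6% | 4.6% |
| 54:18 (3:1) | 1.24 | 1.6% | 4.4% |

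With 90 women the picture is nearly the same: 11.1% at 22:68, 5.1% at 45:45 and 1.6% at 68:22.

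**Step 5. Sensitivity to the SD ratio.** With a ratio of 1.25 in place of 1.55, simulated type I error at 72 women is 7.9% at 18:54, 6.9% at 24:48, 3.5% at 48:24 and 2.9% at 54:18. With a ratio of 1.1 it is 5.7% at 24:48.

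**The case against.** The strongest reply is that the plan's own assumptions produce no fault. It pairs its unequal SDs with 36 per group, and at that split the standard error is right. A reader might infer that the planned ANCOVA gives wrong standard errors outright, with a type I error of 2% to 11%. The documents do not support that. The range needs splits between 3:1 and 1:3, and they state no expected split. They also do not say which group will be larger, so the test may prove conservative rather than liberal. What remains is that the 1:1 ratio is an input to a calculation and not something the recruitment scheme delivers.

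A second reply is that the SDs may not transfer. They are raw change SDs from a trial of a 12-week exercise programme in refractory hypertension, where a wider spread in the trained arm may reflect varied response to training. Here habitual activity is observed and no programme is assigned. This stands, and it is why the milder ratio is shown.

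A reader might also carry the percentages over to the secondary outcomes, since those models share the weakness. The documents give no SDs for diastolic, daytime, night-time or clinic pressure, so no size can be put on it there.

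Finally, in a non-randomised comparison adjusted only for baseline pressure, confounding may matter more. That is a separate question: a robust standard error does not address it, and adjusting for confounders does not in itself repair a wrong standard error.

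**Conclusion.** The point holds conditionally. The plan names an equal-variance model, its only variability figures for the primary outcome are unequal, and the group sizes are left to observed behaviour. If the groups turn out unbalanced and the planning SDs carry over, the primary p-value and confidence interval are miscalibrated, from about 11% type I error at 1:3 to 1.6% at 3:1, or about 8% to 3% if the SD ratio is only 1.25. If the groups come out near 1:1, or the variances prove similar, there is no material problem.

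This is an inexpensive improvement to make before the data are seen, and not a demonstrated error in the primary result. The HC3 rates describe the variance issue alone; they do not make the group contrast causally valid.

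**What to change.** Add one sentence to Data analysis: the primary ANCOVA will use heteroscedasticity-consistent (HC3) standard errors, and the between-group difference will be reported with the resulting 95% confidence interval. Use the same estimator in the general linear models for the other blood pressure outcomes, for consistency and not because a size has been shown for them. Confirm that the software named in the plan offers the option. Report the analysed group sizes and the residual SD in each group, so that readers can judge whether the choice mattered.

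The cost is small. Point estimates do not change. In the simulations HC3 held type I error between 4.4% and 5.5% for splits from 1:4 to 4:1 at 72 women. With balanced groups it is slightly conservative, about 4.5% against 5.0% for the ordinary model. Fixing the estimator now also removes a choice that would otherwise be made after the split and the variances are known.

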**End events**

1) Termination of pregnancy

2) The following conditions occur: vaginal bleeding, regular and painful contractions, premature rupture of membranes, dyspnea, dizziness, headache, chest pain, muscle weakness affecting balance

3) Other serious clinical diseases which are not suitable for further study.

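### The set labelled intention-to-treat is a complete-case set that removes women for post-baseline events, some of them listed outcomes, and no other population is named for the clinical outcomes

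*Supplement*

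**What the plan says.** All references are to the later protocol in the Supplement, on chronic hypertension. The earlier protocol, on women at high risk of pre-eclampsia, defines the population in the same words.

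- Data analysis, principle: "The analyses will be conducted based on the intention-to-treat principle".
- Data analysis, definition: the population is all patients "with the exception of those who do not complete ambulatory blood pressure measurement and physical activity monitoring at 3-time points for any reason". The examples given are these: "for any reason, such as miscarriage, or preterm birth".
- Data analysis, sensitivity: "Per-protocol set will be performed as a sensitivity analysis". The composition of that set is not given, and no method for missing data is described.
- Outcomes, primary: "the difference in 24-hour ambulatory systolic blood pressure change from baseline during the third trimesters of pregnancy", to be analysed by ANCOVA adjusted for baseline blood pressure.
- Outcomes, item 3 lists the incidence of pre-eclampsia. Item 5 lists severe complications and also "fetal death, iatrogenic premature delivery, neonatal asphyxia, NICU".
- Grouping scheme: women are placed in the light or moderate activity group from one week of accelerometry at 11 to 13+6 weeks. There is no randomisation.
- End events: termination of pregnancy, and a list of symptoms: "vaginal bleeding, regular and painful contractions, premature rupture of membranes, dyspnea, dizziness, headache, chest pain, muscle weakness affecting balance".

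**The concern.** An intention-to-treat set keeps everyone in her baseline group whatever happens later. This one does the reverse: whether a woman is analysed is settled by what happens to her after classification. Three consequences follow.

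1. The reasons for removal are not neutral for blood pressure. The Background says that ending the pregnancy is to be considered when hypertension cannot be controlled. Some women with a poor blood pressure course may therefore deliver before the third-trimester recording and leave a blood pressure analysis. Because the groups were formed by observed activity, equal dropout cannot be presumed.
2. Fetal death and iatrogenic premature delivery are listed outcomes, while miscarriage and preterm birth are named grounds for removal. With no other population named, such events before the third monitoring point take the woman out of both numerator and denominator. The plan also promises relative risks without saying over whom.
3. The rule asks for more data than the primary contrast uses. Group is fixed by first-trimester accelerometry, and the ANCOVA needs baseline and third-trimester ABPM. A woman with all of these is still dropped if, say, her second-trimester accelerometry is missing.

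At stake are the validity of the primary estimate, the clinical event rates, and a label that readers take as a safeguard.

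**Working it through.** **The plan's own figure.** Inputs from Data analysis: change of -7.3 (SD 12.7) against +1.1 (SD 8.2) mmHg, two-sided 0.05, 90% power, 20% attrition.

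- Difference: 1.1 - (-7.3) = 8.4 mmHg.
- Pooled SD: sqrt((12.7² + 8.2²)/2) = sqrt(114.265) = 10.69 mmHg.
- Two-sample t-test power (noncentral t): 0.8998 at 35 per group and 0.908 at 36. The plan's 36 per group is reproduced.
- Recruitment: 72/0.80 = 90.

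The plan's own attrition figure therefore allows for 90 - 72 = 18 women outside the set called intention-to-treat. The allowance protects power. It does nothing about which women are lost.

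**What the rule requires and what the contrast needs.** The rule requires 2 recordings × 3 time points = 6 per woman. The primary contrast needs 3: first-trimester accelerometry, baseline ABPM and third-trimester ABPM.

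**Bias by direct arithmetic.** Let p be the dropout share in a group, and D the mean SBP change in dropouts minus that in completers, taken as equal in both groups. The full-group mean is the completers' mean + pD, so the completers' mean is too low by pD. For moderate minus light:

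completers' difference = true difference + D × (p_light - p_moderate)

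D and the split between groups are assumptions, because the documents give neither. Both splits average to the plan's 20%.

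| Dropout, moderate/light | D = 10 | D = 15 | D = 20 |
|---|---|---|---|
| 15% / 25% | 1.0 | 1.5 | 2.0 |
| 10% / 30% | 2.0 | 3.0 | 4.0 |
| 20% / 20% | 0 | 0 | 0 |

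Entries are mmHg. With more dropout in the light group, an apparent benefit of moderate activity shrinks. With the split reversed, it is inflated by the same amount.

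**Bias from a latent-severity model.** Dropout occurs above a threshold of a latent severity that correlates 0.3, 0.5 or 0.7 with SBP change (SD 10.69). These correlations are also assumed.

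- No true difference, 10% against 30% dropout: completers' means fall by 0.63 and 1.59 mmHg at correlation 0.3, and by 1.46 and 3.72 at 0.7. The spurious difference is 0.97, 1.61 and 2.26 mmHg at the three correlations.
- The implied D is the fall divided by p: 0.63/0.10 = 6.3 and 1.59/0.30 = 5.3 at correlation 0.3; 1.46/0.10 = 14.6 and 3.72/0.30 = 12.4 at 0.7. The 4 mmHg entry in the table (D = 20) thus needs a stronger link than this model reaches.
- True difference -8.4, one common threshold, 20% overall dropout: completers show -8.1, -7.5 and -6.7 mmHg. At 10% overall they show -8.2, -7.8 and -7.3. This is attenuation; at 20% and correlation 0.7 the dropout is 12.5% against 27.5%.
- No true difference, equal dropout: no bias.

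**The case against.** The best case for the plan is that groups are formed by observed activity, so no randomisation is broken; that the exclusion is stated openly straight after the principle; and that 20% attrition is budgeted. All three are true. None makes a completers' set represent the women who were classified, and the budget covers numbers, not selection.

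Other points stand and limit the finding.

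- A reader might infer that most fetal deaths and preterm deliveries vanish from the analysis. The text does not support that. It gives no week for the third-trimester ABPM (only the PLGF sample is dated, at 32 to 36+6 weeks), and women who deliver preterm after that recording stay in. The share lost cannot be computed.
- Adverse events are to be reported and safety summarised by group, with no stated restriction to completers. The supportable charge on clinical outcomes is that no population other than the completers' set is named, not that under-counting is certain.
- A reader might infer that symptoms such as "dyspnea, dizziness, headache, chest pain, muscle weakness affecting balance" end data collection. The End events section does not say so.
- A reader might infer that the per-protocol set is a further subset and so blind to this bias. It would usually be narrower, but it is undefined. What can be said is that nothing in the plan shows it would test the exclusion.
- One could multiply six completion rates to project a heavy loss of women. That assumes independent recordings, whereas ABPM and accelerometry are listed together for the same follow-up periods and would tend to be missing together.
- Not every preterm birth or miscarriage is driven by blood pressure.
- A mixed model assumes data are missing at random, so it does not by itself remove bias if loss depends on unobserved blood pressure.

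**Conclusion.** The definition is wrong as written and should be changed before analysis. It is a complete-case set under an intention-to-treat label. It selects on post-baseline events that are listed outcomes or may follow from uncontrolled blood pressure, and it discards women whose primary data are complete.

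The size of the bias in SBP is conditional. It is about 1 to 4 mmHg under assumed 15/25% to 10/30% dropout and a 10 to 20 mmHg excess in dropouts, and about 1.0 to 2.3 mmHg in the latent-severity model with 10/30% dropout and no true effect. It is zero with equal dropout and no true effect. The direction follows whichever group loses more women. For scale, the planned difference is 8.4 mmHg, and the Background cites systolic reductions of 2 to 5 mmHg with exercise in normotensive adults. It would go too far to say that the primary result is certain to be biased. The plan simply neither addresses differential dropout nor provides a way to detect its effect.

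**What to change.** - Define the main set as all women classified at 11 to 13+6 weeks who have a baseline ABPM, analysed by baseline group. Do not require follow-up accelerometry.
- Analyse second- and third-trimester SBP change in a repeated-measures mixed model (group, visit, group × visit, baseline SBP), with the third-trimester contrast as primary. Any woman with at least one follow-up ABPM then contributes.
- Add a delta-adjusted sensitivity analysis, with imputed values shifted by a stated range of mmHg, for women without a third-trimester ABPM. It is needed because the mixed model assumes data are missing at random.
- Count pre-eclampsia, fetal death, preterm delivery and safety events in all enrolled women, and state that denominator for the relative risks.
- Rename the present set complete-case and keep it as a sensitivity analysis. Define the per-protocol set. Report dropout by group with reasons.
- State in the End events section whether such an event stops data collection. No change to clinical management is proposed.

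Cost: revised wording, somewhat more analysis, and abstraction of outcomes from medical records the plan already keeps. No extra patients or recordings are needed. The downside is one of interpretation: for women delivered before the third-trimester ABPM, the estimate refers to a hypothetical continued pregnancy, and the plan should say so.
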